### Recruitment procedures

Patients will be considered for enrolment at four tertiary Canadian academic hospitals (The Ottawa Hospital, Centre Hospitalier de l’Université de Montréal, Centre Hospitalier Universitaire de Sherbrooke, and Vancouver General Hospital). All patients considered for elective liver resection will be seen by an attending surgeon in the outpatient clinic and assessed for study eligibility. Once the patient has provided informed consent for surgery, they will be screened for trial eligibility. Written informed consent will be obtained by study coordinators. Informed consent forms will be available in French and English. Figure 1 shows the schedule of enrollment, interventions, and assessments throughout the trial.

**Fig. 1 Fig1:**
[figure not shown]
Schedule of enrollment, interventions, and assessments. POD, postoperative day; Hx, history; DM, diabetes mellitus; AIDS, acquired immunodeficiency syndrome; CKD, chronic kidney disease; CHF, congestive heart failure; MI, myocardial infarction; PUD, peptic ulcer disease; COPD, chronic obstructive pulmonary disease; PVD, peripheral vascular disease; CVA, cardiovascular accident; TIA, transient ischemic attack; PVE, portal vein embolization; Hgb, hemoglobin; INR, international normalized ratio; AST, aspartate transaminase; ALT, alanine transaminase; GGT, gamma-glutamyl transpeptidase; ALP, alkaline phosphatase; CA 19-9, carbohydrate antigen 19-9; CEA, carcinoembryonic antigen; AFP, alpha-fetoprotein; GFR, glomerular filtration rate; CVP, central venous pressure; PPV, pulse pressure variation; MAP, mean arterial pressure; RBC, red blood cell

### Assignment of interventions

#### Sequence generation

Patients will be randomized in a 1:1 allocation ratio to the two arms of the study, with the use of permuted blocks of variable length (2, 4, and 6). Randomization will be stratified by center. The Ottawa Methods Centre (OMC) will prepare the computer-generated randomization sequence. Secure central web-based randomization will allow for the verification of enrolment and eligibility, as well as ensure allocation concealment.

#### Allocation concealment

The use of central web-based randomization with permutated blocks will ensure that individual surgeons and anesthesiologists cannot determine trial allocation ahead of time. Allocation to the experimental or control interventions will take place the day of surgery. The anesthesiologist will reveal the allocation once the patient is considered “anesthesia ready,” which implies that general anesthesia has been administered, and all lines and catheters have been inserted. By revealing the allocation once the patient is in the operating room and under anesthesia, we can ensure that clinical care will not be influenced by trial allocation.

#### Coordination

The trial will be coordinated out of the Ottawa Hospital Research Institute (OHRI). Each study center will have a site investigator and SC. The Ottawa SC will also act as the overall trial coordinator. Each SC will be responsible for the (a) screening and consenting of patients, (b) central randomization of patients in the operating room, (c) proper implementation of trial procedures, and (d) following patients and correctly filling electronic data collection.

### Blinding

Patients will be blinded to the intervention, as allocation will be revealed to the anesthesiology team following induction of general anesthesia. The anesthesiologist will not be blinded, as they will carry out the intervention. The surgeon, surgical trainees, and the nursing team will be blinded to the intervention. Blinding of the surgical and nursing teams will be completed by carrying out all physical steps necessary for HP (including equipment setup) prior to revealing allocation. Blood collection and scripted movements for the control group (including reverse Trendelenburg position) will take place behind large sterile drapes. At the time of re-infusion of the whole blood, collection bags and tubing will remain hidden from view behind the large drapes. Blinding procedures have been successfully implemented in 98% of patients in the feasibility trial [40]. Success was confirmed based on a post-procedural questionnaire administered to surgeons. Because most perioperative transfusions occur once liver surgery is completed, blinding of the surgeon/surgical team is important to maintain objectivity in determining the need for a blood transfusion. Although the anesthesiologist cannot be blinded, the use of a transfusion protocol specific to the operating room environment will ensure that any transfusion administered is appropriate and clinically indicated [54]. At any time during the study, the attending anesthesiologist can choose to unblind the surgeon for safety reasons. Postoperative outcome assessors will also be blinded to the intervention.

### Data collection methods

#### Assessment and collection of outcomes

Case report forms (CRFs) were created in collaboration with the surgical and anesthesiology teams to capture all relevant study data. The CRFs consist of (1) demographics and medical history details, (2) intraoperative data—surgeon, (3) intraoperative data—anesthesiologist, and (4) postoperative data. These will contain source data. These CRFs are incorporated into an electronic data capture system (EDCS) set up by the OMC. The forms were informed by feasibility trial conducted prior to PRICE-2 [40].

The surgeon, anesthesiologist, and SC will be responsible for the completion of specific sections of the CRFs. The surgeon and anesthesiologist will fill out their respective intraoperative data. The SC will collect demographic data, medical history, and postoperative data.

#### Training

Given that HP is commonly employed at all study sites, no additional training is required, as both surgical and anesthesiology teams will be performing tasks that are within their scope of practice. Training will be provided with respect to study procedures.

#### Intervention and patient compliance

The intervention will be administered in the operating room while the patient is undergoing liver surgery and general anesthesia. Patient compliance is thus not a significant issue to consider. Compliance with the assigned intervention will be monitored carefully. Compliance with the experimental intervention will require that the patient receive HP at a targeted volume of 7–10 mL/kg. *Partial compliance* will be defined as receiving an incomplete (<7 mL/kg) or excessive (>10 mL/kg) phlebotomy. *Non-compliance* will be defined as not receiving the allocated trial intervention (crossover). This can include patients randomized to the experimental intervention who do not receive HP, or patients randomized to the control intervention who receive HP due to perceived excessive blood loss during surgery. In the feasibility trial, there was no case of non-compliance [40]. Partial compliance is expected to be a rare occurrence, as all study sites have significant experience with using HP in clinical practice. In the feasibility trial, partial compliance with HP occurred in less than 5% of cases. Modifications were made to the technical aspects of the protocol to simplify whole blood collection. The PRICE-2 sample is adjusted to reflect partial compliance in 5% of patients.

Cell salvage can sometimes be used to avoid allogeneic RBC transfusions in usual practice [64]. Cases of liver resection where cell salvage is intended to be used are contraindicated in this trial. It is possible that surgeons may elect to use cell salvage in the case of major intraoperative hemorrhage. Surgeons are advised not to do so under the protocol and no such case occurred in the pilot trial. In the event of unplanned cell salvage use, any blood that is retrieved from the operative field and transfused will be coded as a perioperative RBC transfusion event towards the primary outcome, as it is reasoned that the unintended use of emergency cell salvage was likely utilized by the team due to major blood loss to avoid excessive allogeneic transfusions. On the contrary, blood that is salvaged but not transfused will not be considered as a transfusion event.

#### Loss to follow-up

Losses to follow-up to 30 days are not expected following liver surgery. All patients are carefully monitored in hospital for an average of 5–7 days, followed by 1–2 prescribed clinic visits within 3 weeks of discharge.

### Data management

Patients will be identified by a participant ID number on all study documents and electronic databases. All sites will keep any hard copy study documents in locked and secure drawers at their respective sites. For each study patient, relevant preoperative, intraoperative, and postoperative data will be collected and entered into CRFs within the EDCS. Data quality and accuracy will be routinely checked by the trial coordinator.

### Statistical analysis

Our analyses will estimate a modified intention-to-treat effect, such that patients who were randomized in the operating room but did not undergo liver resection due to unresectability will not be included in the analyses. A blinded committee of liver surgeons will adjudicate each post-randomization exclusion. This will ensure that only cases of liver resection abandoned due to unresectability will be excluded from analysis. All other patients who have had protocol deviations (e.g., having an unplanned minor rather than major resection) or crossover (e.g., inability to achieve a full 7–10 mL/kg phlebotomy) will be analyzed within their allocated arm based on an intention-to-treat principle.

Continuous variables will be reported using means and standard deviations, or medians and interquartile ranges, as appropriate. Categorical variables will be reported as frequencies and percentages.

For the primary outcome of 30-day cumulative incidence of any perioperative RBC transfusion, the risk ratio and risk difference will be presented with their respective 95% confidence intervals. Both unadjusted and adjusted effect estimates will be presented. We will fit multivariable generalized linear models using generalized estimating equations (GEE) with an exchangeable correlation matrix with model-based (non-robust) standard errors to estimate an adjusted risk ratio and relative risk, accounting for center effect (clusters). We will incorporate important prognostic covariates (age, sex, preoperative anemia, indication for surgery, magnitude of liver resection, extra-hepatic procedures). Although safeguards are in place to ensure complete data acquisition throughout the trial, missing data for covariates will be handled using multiple imputations by chained equations, where multiple imputed datasets will be pooled to generate final estimates using Rubin’s rules. We will also conduct a complete case analysis to evaluate the potential effect of the missing at random assumptions underlying missing data. Hypothesis testing for the primary endpoint will be carried out at a two-tailed alpha level of 0.05.

For secondary outcomes, both unadjusted and adjusted measures of effect will be presented. Risk ratios and mean differences with 95% confidence intervals will be presented for dichotomous and continuous data, respectively. We will use similar models with GEEs and model-based (non-robust) standard errors to generate adjusted effect estimates, incorporating the same set of covariates as for the primary outcome. For secondary outcomes and analyses, no adjustment will be made for multiplicity.

Subgroup analyses will be conducted based on known risk factors for transfusion in liver surgery: preoperative anemia (larger treatment effect expected with anemia), indication for surgery (larger treatment effect expected with primary liver cancers), and magnitude of liver resection (larger treatment effect expected for extended resections) [61]. An interaction test will be used between each subgroup variable and the treatment group within GEEs estimating risk differences. Published criteria will be used to evaluate the plausibility of the subgroup effects [65].

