While preliminary observations and cohort studies suggest a benefit from HP in liver surgery, it is unclear whether the observed reduction in RBC transfusion is truly attributable to this intervention [46–48]. It is also unknown whether any observed reduction in RBC transfusion will translate into improvement in other perioperative outcomes such as the ease of surgical resection, postoperative complications, or surgical mortality. Finally, more rigorous acquisition of safety data is required. These considerations highlight the need for a definitive randomized controlled trial.

It is hoped that the current trial, summarized in the following protocol, will provide robust evidence of effectiveness of HP in preventing RBC transfusion in liver surgery. As one of the largest trials ever carried out in this patient population, a superiority result would have an immediate impact on the treatment of patients undergoing liver surgery and influence worldwide practice. On the contrary, if the trial fails to demonstrate effectiveness, then this intervention can be abandoned, as the question will have been answered definitively.

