HP will be carried out using standard transfusion medicine precautions for the handling of blood products. Whole blood collection bags will be obtained and appropriately labelled with the patient’s name and hospital identifier. Blood tubing, tubing clamps, and a digital scale will be available in the operating room. HP can be carried out using any vascular access route, at the anesthesiologist’s discretion. Most commonly, blood will be withdrawn from the central venous catheter (CVC), although other options include a 14-gauge antecubital IV (or other large proximal vein/IV caliber), a large-bore central rapid infusion catheter, or an arterial catheter. HP should be initiated and completed prior to the onset of liver parenchymal transection, following trial allocation. Strict aseptic technique will be maintained. The blood tubing system must remain closed and sealed to prevent backflow of air or other potential contaminants. The target blood volume will be determined and translated into weight. This weight of whole blood will then be phlebotomized using a dedicated zeroed scale. If necessary, Trendelenburg position can be used to maximize venous return. Blood collection bags should be frequently and gently agitated to facilitate mixture with the citrate phosphate dextrose adenine (CPDA) anticoagulant. Like other blood products, whole blood bags should be placed in a dedicated transfusion medicine cooler once collected. Collected blood must be re-infused within 8 h if kept in a cooler, or within 4 h if kept at room temperature.

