### Sample size

A review of observational data from The Ottawa Hospital collected between 2010 and 2016 suggests that the cumulative incidence of any perioperative blood transfusion among patients undergoing liver resection is 24% (*n*=316) [41]. Similarly, data from 85 participating NSQIP hospitals in 2013 documented a transfusion incidence of 22% (*n*=2448) [9], whereas a Canadian multicentre collaborative documented 26.5% (*n*=1287) [61]. Our group has documented a transfusion rate of 11.1% in an observational cohort of 45 patients with HP [41]. PRICE-2 is powered to detect a clinically important decrease in perioperative 30-day blood transfusion incidence of 20 to 10% with HP, at 80% power and 5% alpha error (199 patients per arm). A relative risk reduction of 50% has been previously targeted in other transfusion trials in major abdominal surgery [62]. PRICE-2 will include one Haybittle-Peto interim analysis, which does not require sample size adjustment. Allowance is made for a 5% rate of partial protocol compliance or non-compliance in the intervention arm, yielding an 11% increase in total sample size based on the Lachin formula [63]. This trial will thus recruit until 440 patients have been randomized and have had a liver resection after excluding patients that were enrolled and randomized but who did not undergo a liver resection due to disease progression and unresectability identified at surgery (modified intention-to-treat analysis).

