### Data monitoring

The PRICE-2 Steering Committee will be comprised of the principal investigator (PI), all co-investigators (Co-I), and the trial coordinator. The Steering Committee will communicate regularly and will meet as needed. The Committee will implement the trial, review recruitment milestones, and manage any evolving concerns related to trial procedures. An independent DSMB will be appointed and will have expertise in surgery, anesthesiology, biostatistics, and clinical trials. The roles, responsibilities, and reporting of the DSMB, including the interpretation of the interim analysis and adverse events, will be adapted from the DAMOCLES Charter [66].

Three interim analyses will be completed and reported to the Data Safety Monitoring Board (DSMB). The first interim analysis will take place after 100 patients and will examine accrual and adverse events data. The second interim analysis will be conducted after 200 patients and will examine accrual, adverse events, and the primary efficacy outcome. A conservative Haybittle-Peto boundary (*p*<0.001) [67] will be utilized. The third interim analysis will be conducted after 300 patients and will examine accrual and adverse events. The final analysis will be conducted once all 440 patients have been randomized, have had a liver resection, and have been followed to 30 days following surgery, based on the modified intention-to-treat principle.

Study site monitoring will take place remotely at the start of recruitment for each site, as well as upon completion of accrual. Ongoing data monitoring will be conducted and data queries that arise, as well as any issues related to incomplete data, will be addressed on an ongoing basis with study sites. Finally, a formal trial audit plan has been created. A formal audit of the trial will be conducted by the study sponsor and will include complete review of the coordinating center study file, review of a small proportion of participant records, and review of the study files of participating sites.

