The PI or co-investigators will determine if any serious and unexpected adverse events occur from randomization to postoperative day 30. The SC, PI, or co-investigators will examine changes in laboratory values, vital signs, and clinical data, and will determine if the changes are clinically important and different from what is expected during treatment of participants having undergone hepatic surgery and general anesthesia. As perioperative complications represent an important secondary outcome in this trial, adverse events (AEs) will be carefully monitored and recorded. AEs can generally be described as any unfavorable and unintended sign, symptom, or disease temporarily associated with the treatment, whether or not related to the study treatment.

For this trial, any surgical, medical, or anesthesia-related AE that deviates from the usual postoperative course of patients undergoing major liver resection will be collected and recorded in the study AE Source Form by the PI, Co-I, or SC. The PI or Co-I will then assign a grading to this AE based on the Clavien-Dindo classification of perioperative complications [57]. The following will not be considered AEs:*Intraoperative*: bleeding (unless deemed unusually severe by the surgeon), hypotension (unless deemed unresponsive to usual mitigation strategies), oliguria*Postoperative*: pain, hypotension (unless deemed unresponsive to usual mitigation strategies), oliguria (unless associated with acute kidney injury), nausea or vomiting (unless related to ileus or obstruction, or if refractory), sore throat, muscle aches, pruritus, chills, chest pain (unless deemed to be related to a defined AE such as acute coronary syndrome), anemia not requiring transfusion, electrolyte disturbances (unless refractory to usual replacement therapy)

Any AE that is graded as Clavien-Dindo grade 3a or greater will be considered a severe adverse event (SAE). SAEs will be recorded on the study SAE Case Report Form. All SAEs will be further assessed by the PI or Co-Is for expectedness and relatedness to the study procedures. On that basis, unexpected SAEs will be reported to the REB.

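### The modified intention-to-treat exclusion is written for all analyses, so patients found unresectable, some possibly already phlebotomized, leave the final comparisons of adverse events and mortality

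*Protocol article*

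**What the plan says.** The Statistical analysis section opens with the population rule: "patients who were randomized in the operating room but did not undergo liver resection due to unresectability will not be included in the analyses". It names no outcome to which the removal is limited. A blinded committee of liver surgeons adjudicates each exclusion, and all other deviations stay in the allocated arm.

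The same population appears in two other places. Under Sample size, the 440 counts resected patients only and sets aside those who "did not undergo a liver resection due to disease progression and unresectability identified at surgery (modified intention-to-treat analysis". Under Data monitoring, the final analysis takes place once all 440 "have had a liver resection, and have been followed to 30 days following surgery, based on the modified intention-to-treat principle".

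The Secondary outcomes section lists adverse events, end-organ ischemic complications and mortality at 30 and 90 days. The Statistical analysis section gives secondary outcomes models similar to the primary one and no population of their own.

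On timing, the Allocation concealment section has the anesthesiologist reveal the allocation once general anesthesia is established and all lines are in. The Experimental intervention section adds: "HP should be initiated and completed prior to the onset of liver parenchymal transection, following trial allocation".

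On safety, the Background says "Finally, more rigorous acquisition of safety data is required". The Adverse events section says: "The PI or co-investigators will determine if any serious and unexpected adverse events occur from randomization to postoperative day 30".

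**The concern.** Leaving out patients who turn out to be unresectable is a reasonable choice for transfusion. The question there concerns resected patients, the surgeon is blinded, and a blinded committee decides each exclusion.

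The same choice does not suit safety. The hazards of HP that the article lists under Adverse events are reduced organ perfusion, clerical error with the collected blood, and bacterial contamination. All of them begin with the phlebotomy and none needs a completed resection. A patient who is phlebotomized and then not resected carries these risks without the possible benefit. Anyone adopting HP will also have to commit to it before resectability is certain, so the useful safety question covers everyone allocated to it.

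At stake is whether the final report answers that question. The article gives safety as one of its reasons for a definitive trial, yet its population rule narrows the safety comparison to a subset defined after the intervention may have been given.

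**Working it through.** **The plan's own figure.** Inputs from Sample size and Statistical analysis: 20% versus 10%, 80% power, two-sided alpha 0.05.

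- Per arm, pooled variance: n = [1.960 × √(2 × 0.15 × 0.85) + 0.842 × √(0.20 × 0.80 + 0.10 × 0.90)]² / 0.10² = 199, as stated.
- Inflation for 5% non-compliance: 398 / 0.95² = 441.0, a factor of 1.108. The article states 11% and 440.

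These figures are sound. The 440 is a count of resected patients, so the number randomized will exceed it by the number excluded.

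**Can an excluded patient have been exposed?**

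1. Allocation is revealed in the operating room, after induction and line placement (Allocation concealment).
2. HP takes place between that moment and the start of transection (Experimental intervention).
3. Unresectability is identified at surgery (Sample size).

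Steps 2 and 3 can fall in the same interval, and the article does not fix their order. Phlebotomy before the resection is abandoned is therefore possible, but not certain for any given patient.

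**Does the exclusion reach safety outcomes?** The rule removes these patients from the analyses without qualification. Adverse events and mortality are secondary outcomes. Secondary outcomes are given no other population, and the final analysis is placed on the modified intention-to-treat basis. As written, it does reach them.

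**How many patients?** The article gives no unresectable share u, so a range is assumed. Randomized = 440 / (1 − u); excluded = randomized − 440; HP arm = half of the excluded, by 1:1 allocation.

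| Assumed u | Randomized | Excluded | HP arm, about |
|---|---|---|---|
| 2% | 449 | 9 | 4 to 5 |
| 5% | 463 | 23 | 12 |
| 10% | 489 | 49 | 24 |
| 15% | 518 | 78 | 39 |

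An unknown part of the last column would have been phlebotomized.

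**Which way would the result move?** As an illustration with assumed counts, take 4 ischemic events among 220 resected HP patients (1.8%) and 24 excluded HP patients (u = 10%).

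- No events among the 24: 4/244 = 1.6%.
- One event: 5/244 = 2.0%.
- Two events: 6/244 = 2.5%.

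The control arm would change as well. With rare events, one or two cases shift the rate, and nothing in the article says in which direction.

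**The case against.** The strongest reply is that a journal article condenses a fuller protocol, and that a safety set is often defined there or in the statistical analysis plan. The population sentence also describes what the effect estimates target and sits just ahead of the primary-outcome models. A separate safety tabulation elsewhere cannot be ruled out. That much stands, but the point does not depend on something missing: the article states a rule, and the rule as worded takes in every analysis.

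A reader might go further and infer three things that the article does not support.

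- *That harm is understated.* This would require excluded HP patients to have more events than resected ones. They have no completed resection, so their risk could be lower, and including them could dilute a signal. Blinded surgeons and blinded adjudication should also keep exclusions similar between arms.
- *That these patients' events go unseen.* Capture of serious and unexpected events runs from randomization, and unexpected serious events go to the ethics board, with no condition that a resection took place.
- *That the data safety monitoring board sees only resected patients.* The interim safety reviews after 100, 200 and 300 patients have no defined population. Only the final analysis is tied to the modified intention-to-treat principle.

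Blinded adjudication guards against selective exclusion. It does not return the events of correctly excluded patients to the comparison.

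**Conclusion.** The point holds for the final between-arm comparisons of adverse events, ischemic complications and mortality. On the stated rule, patients allocated to HP who may already have been phlebotomized drop out of those comparisons when the resection is abandoned, although serious and unexpected events in them are captured. For the interim safety reviews the population is open rather than wrongly set.

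The size rests on an assumed unresectable share. At 5% to 15%, about 23 to 78 randomized patients are excluded, about 12 to 39 of them in the HP arm. The number actually phlebotomized and the direction of any bias are unknown.

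A reader might also conclude that the efficacy exclusion is unsound or that an all-randomized transfusion analysis is required. Neither follows: the objection concerns only the extension of the rule to safety. The primary inference and the sample size are unaffected. This is an over-broad rule that is worth correcting before analysis, not a threat to the trial's main result.

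**What to change.** Reword the population rule in Statistical analysis so that the modified intention-to-treat exclusion applies to the efficacy outcomes only. Add that adverse events, ischemic complications and 30- and 90-day mortality are analyzed by assigned arm in all randomized patients whose allocation was revealed, with the events of unresected patients also shown separately by arm. State in Data monitoring that the adverse-event reports to the monitoring board use the same set.

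The cost is a short change of text, one extra set of tables, and complete follow-up of unresected patients to 30 and 90 days. No patients are added: 199 per arm, the target of 440 resected patients and the primary analysis stay as they are.

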## Methods and design

### Study design

PRICE-2 is a double-blind multicenter randomized controlled trial (RCT) to evaluate the superiority of HP over usual care. Patients will be randomly allocated to the intervention (HP + usual care) or to the control (usual care). Enrolment will occur at four Canadian academic liver surgery hospitals. Eligible patients that provide consent will be randomized to either of the two study arms in a 1:1 allocation ratio. Apart from the trial intervention, management of patients prior, during, and after liver surgery will be at the discretion of individual practitioners. The trial has been registered publicly at ClinicalTrials.gov since August 2018 (NCT03651154). The trial protocol will be reported in accordance with the Standard Protocol Items: Recommendations for Interventional Trials (SPIRIT) guidelines (Additional file 1).

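### The adjusted primary analysis names one effect measure twice, ties the 0.05 test to none of four estimates, and bases the risk ratio on a four-centre GEE that can be conservative or fail to fit

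*Protocol article*

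**What the plan says.** The primary outcome is whether a patient receives any allogeneic red-cell unit within 30 days. Under Statistical analysis, the protocol article says that a risk ratio and a risk difference will be given with 95% confidence intervals, and that "Both unadjusted and adjusted effect estimates will be presented". That makes four estimates.

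The adjusted model is a generalized linear model fitted by "generalized estimating equations (GEE) with an exchangeable correlation matrix with model-based (non-robust) standard errors to estimate an adjusted risk ratio and relative risk", with centres as the clusters and six named prognostic covariates. The paragraph ends: "Hypothesis testing for the primary endpoint will be carried out at a two-tailed alpha level of 0.05". It does not say which estimate carries that test.

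Two design facts matter. Patients are the randomised units, and "Randomization will be stratified by center" (Sequence generation). There are four clusters: "Enrolment will occur at four Canadian academic liver surgery hospitals" (Study design).

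**The concern.** Three things in the paragraph are badly fixed.

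- **Wording.** Risk ratio and relative risk are the same quantity. The paragraph opens with a risk ratio and a risk difference, so the model sentence leaves the adjusted risk difference without a model.
- **Test.** One alpha level is stated for four estimates. If the deciding estimate is not fixed in advance, the one that crosses 0.05 can be chosen afterwards.
- **Model for the risk ratio.** With model-based standard errors, inference rests on the working variance and on a correlation estimated from four centres. A risk ratio needs a log link. The usual working families are Poisson, whose variance is too large for a binary outcome unless dispersion is estimated, and log-binomial, which may not converge. The section fixes the correlation structure and the type of standard error, but not the family or dispersion that decide how they behave.

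This is the trial's only confirmatory comparison. At stake are some power and a modest amount of alpha.

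**Working it through.** **Step 1: the plan's own sample size.** Inputs from Sample size: 20% against 10%, two-sided 5%, 80% power.

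n per arm = [z(0.975)·√(2·p̄·(1−p̄)) + z(0.80)·√(p1(1−p1) + p2(1−p2))]² / (p1−p2)², with p̄ = 0.15
= [1.960·√0.255 + 0.842·√0.25]² / 0.01 = (0.990 + 0.421)² / 0.01 ≈ 199.

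The factor for 5% non-compliance is 1/(1−0.05)² = 1.108, and 398 × 1.108 = 441 against the stated 440. Both figures reproduce. By the same formula, 220 per arm gives 83.8% power with full compliance, and 79.4% if the 10-point difference shrinks by 5% to 9.5 points.

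**Step 2: the wording.** The results sentence pairs risk ratio with risk difference. The model sentence pairs risk ratio with relative risk. Later in the section, subgroup interactions are tested in GEEs for risk differences, while dichotomous secondary outcomes are reported as risk ratios. No scale can be inferred as primary.

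**Step 3: four estimates, one alpha.** Four independent tests would give 1 − 0.95⁴ = 18.5% error. These four are highly correlated, because all test equality of the same two risks. In simulation, at least one of the four fell below 0.05 under the null in 6.5–7.0% of trials (6.6% under a second set of assumptions).

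**Step 4: why unit-dispersion Poisson is conservative.** Poisson variance is p, and the true variance is p(1−p). The standard error is therefore too large by 1/√(1−p): 1.085 at p = 0.15 and 1.118 at p = 0.20. Under a null risk of 20% the effective critical value is 1.96 × 1.118 = 2.19, a two-sided error of about 2.8%.

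**Step 5: simulation.** 440 patients were randomised individually in blocks within four centres, with control risk about 20%. The following are assumptions, not figures from the document:

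- centre sizes 200/130/60/50 with four covariates and centre SD 0 or 0.4 on the logit scale (4,000 trials per scenario); or
- centre sizes 200/140/70/30 with six covariates and centre log-odds from −0.3 to +0.3 (2,500 null and 1,500 alternative trials).

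The ranges below cover these runs and a further set of the same kind. Power assumes full compliance.

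| Analysis | Type I error | Power |
|---|---|---|
| Unadjusted risk difference or ratio | 4.8–5.2% | 84–85% |
| Adjusted difference, GEE, identity link, model-based SE | 4–5.5% | about 85% |
| Adjusted ratio, Poisson GEE, dispersion estimated, model-based SE | 4.0–5.4% | 83–84% |
| Adjusted ratio, Poisson GEE, dispersion 1, model-based SE | 1.7–3.2% | 76–79% |
| GEE with cluster-robust SE, four centres | about 22% | not interpretable |
| Centre fixed, patient-level robust SE or standardised logistic | 4–5.2% | 85–87% |

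At 4,000 trials the Monte Carlo standard error of a 5% rate is √(0.05 × 0.95/4000) = 0.34 points, so 5.5% is compatible with 5%.

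The log-binomial GEE failed in about 8–25% of data sets. That share depends strongly on software: another implementation gave 3–6% outright failures plus fits stopped at the iteration limit, and a third gave 48–81%. Rejection among returned log-binomial fits was 7–9%. Because some of those fits had not converged, this is not a usable error rate. The estimated exchangeable correlation was negative in 34–44% of data sets in the one run that recorded it.

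**The case against.** A reader might infer that non-robust standard errors with four clusters leave the 5% error rate and the 80% power unsecured. The documents and the calculations do not support that. Treatment varies within every centre, so the centre effect largely cancels from the comparison. Model-based errors are near nominal with an identity link or estimated dispersion, and conservative with unit-dispersion Poisson. The sample size reproduces. Within this GEE, the cluster-robust alternative is the one that breaks down. Negative correlation estimates did no visible harm to the error rate.

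It is also fair to say that the second term in the model sentence is evidently a slip for risk difference, that an unseen analysis plan may name the test, family and dispersion, and that the plan nowhere states a rule of success on any of four estimates. The first of these limits the harm but leaves a sentence that needs correcting. The second is why missing model detail alone would not be a finding. However, this article does fix the structure and the standard error, and under two ordinary ways of fitting a log-link model that choice is wasteful or unreliable. The third means that the 6.5–7% is an upper illustration of free choice, not a predicted error rate.

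Centre fixed effects gain little over the identity-link GEE. Their advantage lies with the risk ratio.

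**Conclusion.** The point holds in limited form. The wording is wrong, and the section does not assign the 0.05 test. Free choice among the four estimates would cost about 1.5–2 points of alpha. The adjusted risk ratio as specified gives power of about 76–79% instead of about 85% if Poisson variance is used with dispersion 1, and fails in perhaps 8–25% of data sets if log-binomial is used. With estimated dispersion, or for the risk difference with an identity link, it behaves acceptably.

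Neither inflated type I error from the planned standard errors nor a general loss of the stated power is shown. The sizes rest on assumed centre sizes, centre effects and covariate strengths. The log-binomial failure rate is the least certain figure. The wording fault and the unassigned test rest on the text alone.

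**What to change.** 1. Name one estimate for the two-sided 0.05 test, for example the adjusted risk difference, and call the other three supportive.
2. In the model sentence, replace relative risk with risk difference.
3. Fit centre as a fixed effect (three indicators, matching the randomisation strata). Obtain both measures by standardising a logistic model, or use modified Poisson for the ratio, with patient-level robust standard errors. In the simulations this held about 4–5% error and 85–86% power, and in the run that tracked failures it never failed to fit.
4. If the GEE is kept, state family, link and dispersion for each measure, with dispersion estimated for a Poisson ratio. Do not switch to cluster-robust errors with four centres.

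The cost is analysis wording and code plus three degrees of freedom for centre. No extra patients or data are needed.
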